#### 5.1.2 Dose Regimen assignment

Detailed rules for DR assignment are described in Section 9.9.1 Arms and DLT observation periods.

If the quantity of the initial manufactured CAR T cell product is less than the specified DL, but is otherwise releasable by TCPC, it may be administered as long as the subject meets criteria to

undergo initial T cell infusion (Section 5.5.1 Requirements for initial CAR T cell infusion) and the occurrence is clearly documented in the subject files (see [Section 5.6 Guidelines for Administering the CAR T Cell Product](#)). However, in the absence of a DLT during Courses 1 and 2, such subjects will not be evaluable for DR escalation per Section 9.9.2 Dose Regimen (DR) escalation rules.

If a subject has a releasable CAR T cell product but treatment is suspended (during the mandated period between participants, or while the data are under review by the Data Safety Monitoring Board [DSMB] or Food and Drug Administration [FDA]) and the subject is not medically stable enough to wait until treatment is reinitiated, the subject may receive their CAR T cell product according to the schedule and specific CAR T cell DLs of the maximum DR already deemed tolerable.

Subjects who are removed/withdraw from the protocol prior to receiving CAR T cell product will be replaced to meet statistical guidelines for evaluation of toxicity and feasibility.

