**Figure 5-1 Arm A and B Dose Regimen 1**

[figure not shown]

Subjects enrolled in Arm A and B DR 1 will receive Course 1 consisting of DL 1 on Weeks 1, 2, and 3 followed by a rest during Week 4, with clinical evaluations.

Course 2 will commence for subjects without DLT and who meet criteria for subsequent CAR T cell infusions (Section 5.5.2 Requirements for subsequent CAR T cell infusion and dose modification). Subjects will receive DL 1 on Week 1, DL 2 on Weeks 2 and 3, followed by a rest during Week 4 with disease evaluation, including radiographic restaging.

Following Course 2, subjects meeting criteria for further CAR T cell infusion (Section 5.5.2) may receive additional Courses of therapy until subject meets criteria for removal from protocol therapy, intolerable toxicity, or depletion of available manufactured CAR T cells. The DLs for Courses 3 and beyond will be no higher than DL 2 or the dose which no DLTs were experienced by the subject during Courses 1 and 2. A lower DL may be administered based on availability of CAR T cells, see Section 5.1.2 Dose Regimen assignment. Treatment will be administered on Weeks 1, 2, and 3 followed by a rest week every fourth week. Disease restaging evaluations will occur as indicated in the schedule of procedures.

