## 5.2 Dose-Limiting Toxicity (DLT)

A DLT is an event, defined below, which, in the opinion of the investigator, is possibly, probably, or definitely attributable to the CAR T cell product and which occurs from the time of initial CAR T cell infusion through 28 days following the final CAR T cell infusion. The Maximum Tolerated Dose Regimen (MTDR) will be established by the occurrence of DLTs which occur from the time of initial CAR T cell infusion through 7 days following the final CAR T cell infusion received during Course 2. See Section 9.9.4 Definition and determination of MTDR and RP2DR, for information on establishing MTDR.

The definition of a DLT includes all  $\geq$  Grade 3 Common Terminology for AEs (CTCAE) v5 toxicities **except**  $\geq$  Grade 3 toxicities that are known to be related to CAR T cells [45], listed below.

Exceptions to  $\geq$  Grade 3 DLTs:

- Grade 3 CRS that decreases to  $\leq$  Grade 2 within 72 hours of onset
- $\geq$  Grade 3 hypotension, fever, chills not controlled with medical intervention that decrease to  $\leq$  Grade 2 within 72 hours
- $\geq$  Grade 3 activated PTT, fibrinogen, and/or INR that are asymptomatic and resolve within 72 hours
- $\geq$  Grade 3 hypoglycemia and/or electrolyte imbalance that are asymptomatic and resolve within 72 hours
- $\geq$  Grade 3 nausea and/or vomiting that decrease to  $\leq$  Grade 2 within 7 days

- Arm A and B only: Grade 3 neurological adverse event that decreases to  $\leq$  Grade 2 within 7 days
- Arm C only: Grade 3 neurological adverse event that decreases to  $\leq$  Grade 2 within 21 days (treatment with dexamethasone and/or bevacizumab is allowed)

The definition of a DLT also includes any related toxicity lasting  $> 14$  days which prohibits the subject from meeting criteria for subsequent CAR T cell infusion.

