### **9.9.2 Dose Regimen (DR) escalation rules**

A subject will be considered DR escalation-evaluable if they are evaluable for MTDR DLT and are counted as part of a 3-subject dose escalation Cohort according to the rules described below.

The following rules will be applied separately and independently for each Arm. DLTs are defined in Section 5.2.

*Dose escalation rules using a modified 3 + 3 design for Arms A, B, and C.* DRs are detailed in Section 5.1.3.

1. Escalation and de-escalation decisions will use cohorts of 3 consecutive toxicity-evaluable subjects treated at the same DR
2. The dose escalation route will be similar to a 3+3 design, and will allow expansion on the tentative MTDR if 1 DLTs out of the first cohort of 3 and 1 DLTs out of the second cohort of 3 were observed
  - a. If 0 DLTs out of the first cohort of 3 (0/3) within a DR, and there is a DR available for escalation, it will escalate to the next DR. If there is no DR

available for escalation, then this DR is considered as tentative MTDR and another cohort of 3 will be treated at the current DR.

- b. If 1 DLTs out of the first cohort of 3 (1/3), a second cohort of 3 will be treated and evaluated at the current DR
  - i. If 0 DLTs out of the second 3 and there is a DR available for escalation, it will escalate to the next DR. If there is no DR available for escalation (1 DLT in first 6), the MTDR will be estimated
  - ii. If 1 DLTs out of the second cohort of 3 (i.e. 2 DLT in the first 6), a third cohort of 3 will be treated at the current DR. If there are 0 DLTs in the third cohort of 3, the MTDR will be estimated. If there is 1 DLT in the third cohort (i.e. 3 DLTs in the first 9), a final cohort of 3 will be treated at the current DR and the MTDR will be estimated once all subjects have been evaluated.
- c. If 2 or more DLTs out of any cohort of 3 ( $\geq 2/3$ ) toxicity-evaluable subjects, the current DR will be shut down and the DR will de-escalate to the previous DR. If the first 2 subjects of any cohort of 3 both experience DLTs and the third subject has not received CAR T cells, stop the cohort at 2 subjects and de-escalate to previous DR and the third subject will become the first subject of a new cohort. If there is no DR available for de-escalation (lowest), the arm will be shut down.

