### 9.9.3 Stopping rules

In the event of the following, further T cell infusions will be suspended pending review by the DSMB and consultation with the FDA:

- Death unrelated to disease progression or accidental trauma that occurs within 30 days of CAR T cell administration

To further protect the safety of patients, infusions will also be suspended pending review by the DSMB and consultation with the FDA if the lower bound of a 1-sided 80% exact binomial confidence interval of the discontinuation rate due to medically significant Grade 4 or greater events that are possibly, probably, or definitely attributable to CAR T cells is  $> 10\%$ .

Operationally, any of the following would trigger such a rule: 2 out of the first  $\leq 5$  subjects or 3 out of the first  $\leq 11$  patients or 4 out of the first  $\leq 18$  patients or 5 out of the first  $\leq 24$  have unacceptable toxicity or  $\geq$  Grade 4 AEs that are possible, probably, or definitely attributable to CAR T cells. If the true probability of  $\geq$  Grade 4 AE is 2.5%, the probability of study suspension under the above rule is approximately 0.007; if the true probability is 30%, the probability of suspension is approximately 0.93 (probabilities estimated from 5,000 simulations).

This rule will apply to medically significant (requiring medical intervention)  $\geq$  Grade 4 toxicities that are possibly, probably, or definitely attributable to CAR T cells, with the exception of Grade 4 CRS for  $< 72$  hours, and Grade 4 fever.

If this rule is met, further T cell infusions for all subjects enrolled will be immediately halted. A safety evaluation will be performed and reviewed with the FDA and DSMB prior to resuming any CAR T cell infusions.

Additionally, the Study Chair may shut down a DR at any time due to toxicities observed or efficacy observed at lower DRs.

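### Section 5.1.2 permits infusion during a DSMB or FDA review suspension without excluding the Grade 4+ halt, when Section 9.9.3 bars any infusion

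*Protocol*

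**What the plan says.** **Section 5.1.2 (Dose Regimen assignment)** covers a subject who has a releasable product while treatment is suspended. It names two kinds of suspension: the mandated interval between participants, and the period "while the data are under review by the Data Safety Monitoring Board [DSMB] or Food and Drug Administration [FDA"]. If the subject is not stable enough to wait, "the subject may receive their CAR T cell product according to the schedule and specific CAR T cell DLs of the maximum DR" so far judged tolerable. No type of review is excluded. The section points to 9.9.1 and 9.9.2 but not to 9.9.3.

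**Section 9.9.3 (Stopping rules)** suspends infusions pending DSMB review and FDA consultation when the Grade 4+ boundary is crossed. It continues: "If this rule is met, further T cell infusions for all subjects enrolled will be immediately halted". On restarting: "A safety evaluation will be performed and reviewed with the FDA and DSMB prior to resuming any CAR T cell infusions". It contains no exception and does not mention 5.1.2.

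**How a DR is cleared.** Section 9.9.2 states: "The following rules will be applied separately and independently for each Arm". Under Section 5.2, the maximum tolerated dose regimen (MTDR) rests on dose-limiting toxicities (DLTs) from the first infusion "through 7 days following the final CAR T cell infusion received during Course 2". Treatment can go on after that: "subjects meeting criteria for further CAR T cell infusion (Section 5.5.2) may receive additional Courses of therapy" (Section 5.1.4, with similar text for the other regimens).

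**The concern.** The two sections give different answers to the same clinical question. During a Grade 4+ halt, treatment is suspended and the data are with the DSMB and FDA, which is the situation 5.1.2 describes. A clinician with a deteriorating child and a released product would find a written permission in 5.1.2 and an absolute bar in 9.9.3, with nothing to say which governs.

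Acting on the permission would expose a subject before the safety signal has been evaluated. The cap at a regimen already judged tolerable may not protect that subject, because the regimen chosen could be the one whose own later-course Grade 4+ events caused the halt.

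**Working it through.** **1. Does a Grade 4+ halt fall within 5.1.2?**

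| Question | Section 5.1.2 | Section 9.9.3, Grade 4+ rule |
|---|---|---|
| When does it apply? | Treatment suspended, including for DSMB or FDA review | Infusions suspended for DSMB review and FDA consultation |
| Who is covered? | A subject too unstable to wait | All enrolled subjects |
| Is infusion allowed? | Yes, at the highest DR judged tolerable | No, until the safety evaluation has been reviewed with the FDA and DSMB |
| Reference to the other section? | None | None |

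The triggers overlap and the instructions differ. The escalation rules in 9.9.1 and 9.9.2 require no DSMB or FDA review. The infusion suspensions that the protocol ties to such review are the two in 9.9.3 (a death, or the Grade 4+ boundary) and the expansion halt in 9.10. Section 5.1.2 lists the between-participant interval separately, so its review clause cannot be read as meaning only that interval.

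**2. Does the cap at a tolerable DR remove the conflict?** No, because the 9.9.3 halt applies whatever the DR. The two safety counts also differ:

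- DR clearance is arm by arm, on DLTs up to 7 days after the last Course 2 infusion.
- The Grade 4+ rule counts all subjects together. Its scope sentence begins "This rule will apply to medically significant (requiring medical intervention" and sets no such window.

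Illustrative example (assumed counts):

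- A DR clears with 1 DLT in 6 subjects, and that DLT is a related, medically significant Grade 4 event outside the rule's exceptions.
- Two more of the six have such an event in Course 3, with no more than 11 subjects treated in the whole trial.
- Grade 4+ count: 1 + 2 = 3, which meets the boundary of 3 in the first 11 or fewer. The trial halts.
- DLT rate on which the DR was cleared: 1/6 = 17%, unchanged by the Course 3 events.
- Rate over all courses: 3/6 = 50%.

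**3. How likely is a halt?** Boundaries from 9.9.3: 2 events in the first 5 or fewer, 3 in 11 or fewer, 4 in 18 or fewer, 5 in 24 or fewer. Let a(n, k) be the probability of reaching subject n with k events and no halt yet, at true rate p:

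a(n, k) = a(n−1, k)(1−p) + a(n−1, k−1)p

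After each subject, the mass at or beyond the boundary is removed and added to the halt probability (first halt only). For the first five subjects this reduces to 1 − (1−p)^5 − 5p(1−p)^4; at p = 0.10 that is 1 − 0.5905 − 0.3281 = 0.0815 from unrounded terms.

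| True rate | Within first 5 | Subjects 6–24 | Total by 24 | Stated in 9.9.3 |
|---|---|---|---|---|
| 2.5% | 0.0059 | 0.0017 | 0.0077 | about 0.007 |
| 10% (assumed) | 0.0815 | 0.1019 | 0.1834 | not given |
| 20% (assumed) | 0.2627 | 0.3873 | 0.6501 | not given |
| 30% | 0.4718 | 0.4518 | 0.9236 | about 0.93 |

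(Columns may differ from their sum by 0.0001 through rounding.) The recursion agrees closely with both of the protocol's simulated figures. The first-five share of the total is 78%, 44%, 40% and 51% respectively. Few or no DRs could be cleared that early if events are counted in treatment order, so the column for subjects 6–24 is the more relevant one for 5.1.2.

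**The case against.** **5.1.2 is only a permission.** It sits in a section on choosing a regimen, and 9.9.3 is specific and mandatory, so a careful reader would let 9.9.3 prevail and withhold the infusion. It is true that withholding satisfies both sections, and that the weekly review group (9.11.1) would probably be involved. But precedence is nowhere stated, and the permission is written for the patient who cannot wait, which is when it will be consulted.

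**The review clause has other work to do.** It could apply to the 9.10 expansion halt, which lacks the all-subjects wording of 9.9.3. That is a possible reading and explains why the clause need not be deleted. It does not take the Grade 4+ halt out of the clause.

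**Tolerability may be judged on more than the Course 1–2 count.** Section 9.5 uses toxicities up to 28 days after the final infusion for overall safety and tolerability, and 9.9.3 lets the Study Chair close a DR at any time. Later-course events could therefore be held against a DR. This stands in part: the phrase in 5.1.2 is undefined, so the 1/6 against 3/6 example shows what can happen, not what must. The same Section 9.5 uses the shorter window for escalation and the MTDR, and the halt binds whatever the DR.

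**The halt probabilities do not measure the conflict.** Correct. The recursion also takes outcomes as known in treatment order, so a late event in one of the first five subjects could trigger a halt after a DR has cleared. The split between the first 5 and subjects 6–24 is therefore only indicative.

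**The proposed exception is not in 9.9.3.** Also correct. It is an offered safeguard for unstable patients and can be left out.

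**Conclusion.** The concern holds and should be fixed. Read literally, 5.1.2 permits an infusion that 9.9.3 forbids during a Grade 4+ halt, and the protocol does not say which section governs. This rests on the text alone and on no probability.

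On size, a first Grade 4+ halt within 24 subjects has probability 0.008, 0.18, 0.65 and 0.92 at true rates of 2.5%, 10%, 20% and 30%, assuming independent subjects with a common rate and outcomes known in treatment order. How often an unstable subject with a released product would coincide with a halt cannot be computed, because the protocol gives no rate for it. The claim is limited to the Grade 4+ halt. The death-triggered suspension in 9.9.3 and the expansion halt in 9.10 overlap with 5.1.2 in the same way, but lack the explicit wording about all subjects and any infusion, so they need clarification only.

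**What to change.** Add to Section 5.1.2:

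> This provision does not apply while infusions are halted under the Grade 4 or greater rule in Section 9.9.3; during such a halt no subject is infused until the safety evaluation has been reviewed with the FDA and DSMB, unless both agree in advance to an individual infusion.

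Add a cross-reference to 5.1.2 in Section 9.9.3. If the sponsor wants 9.9.3 kept without exception, drop the final clause. As a clarification, state whether 5.1.2 applies during the death-triggered suspension (9.9.3) and the expansion halt (9.10).

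The cost is one sentence and one cross-reference in an amendment, with no change to sample size or stopping boundaries. The downside is that an unstable subject may have to wait during a Grade 4+ halt, which 9.9.3 already requires; the advance-agreement clause leaves a controlled route for an individual case.

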### **5.1.3 Description of Dose Regimens**

Dose regimens (DR) will be the same for Arms A and B using an intra-patient dose escalation schema with weekly dosing during 3 of every 4 weeks. Arm C will use every other week dosing.

### 5.1.4 Arm A and B Dose Regimens 1 through 3

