**Table 5-1 CAR T Cell Dose Levels**

| Dose Level (DL)  | Dose                        |
|------------------|-----------------------------|
| DL 1 (test dose) | 1 x 10  cells   |
| DL 2             | 2.5 x 10  cells |
| DL 3             | 5 x 10  cells   |
| DL 4             | 10 x 10  cells  |

During the time from apheresis to infusion of CAR T cells, subjects may return to the care of their primary physician and may receive additional cancer-directed therapy (see 5.4 Bridging Therapy). The site team will be notified when the subject's CAR T cell product is released and available so that the CAR T cell infusion may be scheduled.

CAR T cell therapy will be administered on Study Weeks 1 through 3 (Arms A and B) or Weeks 1 and 3 (Arm C) of each 4-week Course. Dosing will start with a test dose (DL 1) at Week 1. Arm A and B, DR 1 will establish the safety of the test dose plus a single DL escalation. Arm C DR 1 will establish the safety of the intermittent administration of the test dose without DL escalation.

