**Figure 5-4 Arm C Dose Regimen 1**

[figure not shown]

Subjects enrolled in Arm C DR1 will receive Course 1 consisting of DL 1 on Weeks 1 and 3 followed by a rest during Week 4, with clinical evaluations.

Course 2 will commence for subjects without DLT and who meet criteria for subsequent CAR T cell infusions (Section 5.5.2). Subjects will receive DL 1 on Week 1 and DL 1 on Week 3, followed by a rest during Week 4 with disease evaluation, including radiographic restaging.

Following Course 2, subjects meeting criteria for further CAR T cell infusion (Section 5.5.2) may receive additional Courses of therapy until subject meets criteria for removal from protocol therapy, intolerable toxicity, or depletion of available manufactured CAR T cells. The DLs for Courses 3 and beyond will be no higher than DL 1 unless a subsequent DR has been cleared for escalation or for selection as the MTDR. In that case, the subject may increase to the highest DL on the subsequent DR. Treatment will be administered on Weeks 1 and 3 followed by a rest week every fourth week. Disease restaging evaluations will occur as indicated in the schedule of procedures.

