### 5.1.6 Treatment Plan Delays

During each Course, the time interval between each CAR T cell infusion will be according to the Schedule of Procedures and based upon the date of the most recent CAR T cell infusion. The end date of each Course will be the date of completion of Week 4 evaluations per the Schedule of Procedures. The start date of each Course will be the date that the Week 1 CAR T cell infusion required evaluations are performed.

Within Course 1 and 2, if a subject does not meet the criteria to receive a CAR T cell infusion ([Section 5.5.2](#)) on the planned infusion day of a Course regardless of attribution to the CAR T cells, the infusion may be delayed no more than 3 weeks from the planned infusion date. If delayed greater than 3 weeks from the planned infusion date, the subject will be removed from

protocol therapy and will not receive further CAR T cell treatment. See [Section 8.1](#) Removal from Protocol Therapy.

Between Course 2 and Course 3, delays due to family/subject preference, investigator discretion, or due to subject recovery from a surgical procedure (e.g., tumor biopsy) are allowed. Following Course 3, only delays due to subject recovery from a surgical procedure (e.g., tumor biopsy) or due to travel disruptions are allowed. During the delay subjects must continue to be followed for concomitant medications (Section 7.8) and adverse events (Section 7.9). Criteria for removal from protocol therapy in Sections 5.5.2 and 8.1 will override family/subject/investigator preference delays as noted above.

Beyond Course 2, subjects must receive at least the Week 1 infusion of any Course but may skip the other scheduled infusions. If a subject does not receive an infusion within 3 weeks of the Week 1 infusion, the next infusion will be considered a new Course. If infusions are delayed, the subsequent pre- and post-visit evaluations/procedures (see [Appendix 2 – Schedule of Procedures](#)) will be timed based upon the next administered CAR T cell infusion. If an infusion is not given, the pre- and post-visit procedures for that infusion are not required. If delay to subsequent infusion is greater than 8 weeks from prior infusion, disease response assessment must be obtained prior to dosing.

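### In the Arm C Schedule, the only numeric limit on how early the Week 3 infusion may be given is 7 days, half the every-other-week interval the protocol prescribes

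*Protocol*

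**What the plan says.** The narrative is consistent about Arm C. Section 5.1.3 states that "Arm C will use every other week dosing", in contrast to weekly dosing in Arms A and B. The text under Table 5-1 gives "Weeks 1 and 3 (Arm C) of each 4-week Course", and each Arm C regimen in section 5.1.5 repeats those two weeks. Spacing is also part of what the arm is meant to test: "Arm C DR 1 will establish the safety of the intermittent administration of the test dose".

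For the number of days, section 5.1.6 points elsewhere: "During each Course, the time interval between each CAR T cell infusion will be according to the Schedule of Procedures", counted "based upon the date of the most recent CAR T cell infusion". In Table 1b, the procedure-window row for the Week 3 infusion carries footnotes f and g. Footnote f times the pre-infusion evaluations (up to 2 days before). Footnote g requires at least 7 days since the previous infusion. Footnote g of Table 1a, for Arms A and B, has the same figure.

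For lateness in Courses 1 and 2, section 5.1.6 is explicit: "the infusion may be delayed no more than 3 weeks from the planned infusion date".

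**The concern.** For Arms A and B, a 7-day minimum equals the prescribed interval. For Arm C it is half of it, so the number that section 5.1.6 sends the reader to does not express the Arm C schedule. No other within-subject minimum is given in the text: section 5.5.2 sets none, the 3-week rule is a late limit, and the 14-day rule in section 9.9.1 is a stagger between subjects.

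What is at stake is regimen fidelity in a small, DLT-driven escalation. Both Week 3 infusions of Courses 1 and 2 fall inside the DLT period used for the MTDR (sections 5.2 and 9.5). The evaluability rules in sections 9.5, 9.7 and 9.9.1 contain no spacing condition. A subject infused early would therefore contribute a full DLT result to a cohort of three. Under section 9.9.2, the difference between 0 of 3 and 1 of 3 decides whether the arm escalates or treats a second cohort.

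**Working it through.** No sample size, power or error rate is involved. The check is which days for the Week 3 infusion satisfy the numeric windows in Table 1b.

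**Inputs.** Let x be the day of the Week 3 infusion and e the day of the Week 2 evaluation, both counted in days after the Week 1 infusion of the same Course (1 or 2).
- Prescribed interval (5.1.3, 5.1.5): Week 1 to Week 3, nominally x = 14.
- Footnote g: x ≥ 7.
- Footnote h: post-infusion evaluation on days 2 to 5.
- Footnote z: 8 ≤ e ≤ 14. The same visit may serve as the Week 3 pre-infusion evaluation if it is within 2 days of that infusion.
- Footnote f: pre-infusion evaluation between days x − 2 and x.
- Assumption: the Week 2 evaluation is done no later than the Week 3 infusion, so e ≤ x.

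**Enumeration.**
- x ≤ 6: fails footnote g.
- x = 7: meets g, but the Week 2 evaluation (day 8 at the earliest) would come after the infusion.
- x = 8 to 13: meets f, g, h and z.
- x = 14: the prescribed day, which also meets all four.

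The early range is therefore days 8 to 13, which is 14 − 13 = 1 day to 14 − 8 = 6 days before plan. The stated floor is 7/14 = half of the prescribed interval.

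**Shared visit.** A visit on day 8 serves both purposes when 8 ≤ x ≤ 8 + 2 = 10. For x = 11 to 13, a shared visit would fall on day x − 2 or later (day 9 at the earliest), still within footnote z.

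**Doses affected (Table 5-1 and 5.1.5).**
- Course 1, Week 3: DR 3 steps from 1 × 10⁷ to 2.5 × 10⁷ cells (2.5/1 = 2.5-fold), and DR 4 from 1 × 10⁷ to 5 × 10⁷ (5/1 = 5-fold).
- Course 2, Week 3: no dose step, but this is the second infusion at the regimen's highest level (2.5, 5 and 10 × 10⁷ cells in DR 2, 3 and 4).

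**After the fix.** With a 14-day minimum, the earliest compliant day is 14. With an illustrative 2-day tolerance it is 14 − 2 = 12. Days 8 to 10 are excluded either way.

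**The case against.** The strongest reply is that the Schedule is the whole table, not one footnote. Table 1b marks Arm C infusions only in the Week 1 and Week 3 columns and has a separate Week 2 column without an infusion. Footnote z itself numbers Week 2 as days 8 to 14. A floor of at least 7 days is compatible with a 14-day plan and does not contradict it. An infusion on day 8 would depart from the narrative, and section 12.6 counts any departure from the study design or procedures as a deviation. There is one site, and compliance is reviewed weekly.

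Most of this stands. A reader might infer that the protocol permits weekly dosing in Arm C. It does not, because the text and the week labels say otherwise. What the reply does not supply is a number: the week label carries no tolerance in days, and the only figure attached to that infusion's timing is the one for the weekly arms.

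Three wider readings are also tempting and should not be made.
- Week 1 infusions of Course 2 and later carry only footnote f, which might look like a further Arm C gap. Table 1a does the same for Arms A and B, and the rest week and the rule that "The end date of each Course will be the date of completion of Week 4 evaluations" provide the separation.
- From Course 3 on, Table 1b has no Week 2 visit, so day 7 would pass the windows. Those infusions lie outside the MTDR period, so they have no bearing on escalation.
- The 21-day allowance for Grade 3 neurological events in Arm C (section 5.2) is a DLT recovery exception and says nothing about spacing.

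**Conclusion.** The point holds as a minor defect limited to footnote g at the Week 3 infusion of Courses 1 and 2 in Arm C. The written minimum is 7 days where 14 are prescribed, so an infusion 1 to 6 days early meets every numeric window while departing from the regimen. Its DLT result would still be counted for that regimen.

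No statistical figure changes. A reader might infer that a 7-day gap is unsafe in Arm C, but the documents contain nothing to show that. They also do not show that an early infusion has occurred.

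The conclusion rests on two assumptions: that the Week 2 evaluation precedes the Week 3 infusion, and that the Arm C regimen figures (5-4 to 5-7), which are not reproduced in the text available, add no day count of their own.

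**What to change.** In Table 1b only, change footnote g so that the infusion is given 14 days after the previous one, with a short early tolerance set by the sponsor (for example −2 days, so day 12 at the earliest). The late limit in section 5.1.6 and footnote z can stay as they are. Table 1a stays unchanged, since 7 days is right for weekly dosing.

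The cost is one footnote edit at the next amendment and slightly less scheduling freedom at the site. Footnote g is also attached to the Week 3 infusion from Course 3 on, so the edit would apply there too, in line with the schedule stated for those Courses: "Treatment will be administered on Weeks 1 and 3 followed by a rest week every fourth week". If the sponsor does intend a 7-day floor for Arm C, the protocol should say so outright.
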